## Abstract

•Assessment of flow rates of the hepatic artery during pancreatoduodenectomy.•Identification of pre- and intraoperative factors influencing liver blood flow.•Relevance of a celiac axis stenosis by pancreatoduodenectomy.

Assessment of flow rates of the hepatic artery during pancreatoduodenectomy.

Identification of pre- and intraoperative factors influencing liver blood flow.

Relevance of a celiac axis stenosis by pancreatoduodenectomy.

## Background

1

Pancreatoduodenectomy remains the oncological treatment of choice for a range of malignant diseases, including ampullary carcinoma, distal cholangiocarcinoma, progressive intraductal papillary mucinous neoplasm, pancreatic adenocarcinoma, and benign diseases such as chronic pancreatitis and biliary duct adenoma [1], [2]. From the oncologic point of view, tumor infiltration might indicate extended arterial or venous resection [3], [4], [5], which require the pancreas to be separated from its supplying vessels, in particular the gastroduodenal artery.

The gastroduodenal artery is a branch of the common hepatic artery along with the proper hepatic artery, which provides most of the liver’s blood supply. Thus, dissection of the gastroduodenal artery disturbs blood supply to the liver during pancreatoduodenectomy. This is usually compensated without postoperative complication or liver ischemia. However, in some patients undergoing extended resections with anatomical variations or unknown coeliac axis stenosis, inadequate blood flow through the hepatic artery can prevent liver perfusion [6], [7]. This is important in pancreatoduodenectomy patients because the gastroduodenal artery is lost, which may cause ischemic complications and postoperative liver perfusion failure [8].

To avoid this, it is highly recommended to perform the clamping test before the artery is resected, to determine whether blood supply is sufficient [7]. Here, the surgeon manually tests the pulsating flow in the proper hepatic artery after clamping the gastroduodenal artery. Such a test is, of course, subjective and depends on the attending surgeon’s perspective. Alternatively, Doppler flowmetry can quantify the expected remaining perfusion from the proper hepatic artery.

There is no well-established algorithm to assess and ensure sufficient blood flow in patients with alternated hepatic artery blood flow. Consistent intraoperative measurement of arterial and portal-venous blood flow to the liver via Doppler flowmetry can assess liver perfusion during pancreatoduodenectomy. The aim of this study is to establish a basis for evaluating liver blood supply during pancreatoduodenectomy. Furthermore, factors influencing arterial blood flow and related postoperative complications will be evaluated and identified.

## Methods and analysis

2

### Study design

2.1

This is a single institutional one-arm prospective exploratory observational clinical trial designed in accordance with the declaration of Helsinki. This study was initiated in April 2018 and is expected to progress for 2 years. The study protocol was registered at the German Clinical Trials Register (registration number: DRKS00014620).

### Patient eligibility

2.2

All consecutive patients undergoing elective pancreatoduodenectomy will be screened for inclusion until 100 patients are enrolled (Fig. 1). To account for patients who do not meet eligibility criteria, patients who refuse to participate, and intraoperative decisions against resection, it was estimated that 150 patients need to be screened.

**Fig. 1 f0005:**
[figure not shown]
Study flow chart. *Numbers are estimated.

#### Inclusion and exclusion criteria

2.2.1

Inclusion criteria are: 1) ≥ 18 years, 2) undergoing elective open partial or total pancreatoduodenectomy, and 3) have given consent to participate in the study. Exclusion criteria are: 1) previous surgery on upper gastrointestinal organs (esophageal resection, gastric surgery, splenectomy, resection of one or more liver segments, liver transplantation, pancreas left resection, and vascular surgery of visceral vessels), 2) liver cirrhosis or other severe liver disease, and 3) bilirubin levels ≥ 15 mg/dl. In patients with pancreatic tumors, it is not always possible to predict whether resection is feasible before surgery. In these cases, an explorative laparotomy is needed to determine the appropriate surgical procedure. If extensive tumor infiltration or metastases are present, surgery cannot be performed and these patients must be excluded from the study.

### Patient recruitment and evaluation

2.3

This study was approved by the Ethics Committee of the University of Heidelberg (S-073/2018). As presented in Fig. 1, all patients scheduled for partial or total pancreatoduodenectomy will be screened for eligibility. Preoperative assessment, including medical history, physical examination, and laboratory evaluations, will be performed according to Table 1.

**Table 1 t0005:** Preoperative parameters to be evaluated in included patients.

Demographic and baseline data	• Gender (f/m) • Age (years) • Body mass index (kg/m^2^) • ASA classification • Medication • Alcohol consumption • Nicotine intake
Comorbidity	• Cardiovascular diseases • Blood coagulation disorders • Liver diseases • Pancreas diseases • Cancer
Previous interventions	• Chemoradiotherapy • Operations
Laboratory data	• Aspartate transaminase (U/l) • Alanine aminotransferase (U/l) • Albumin (g/l) • International normalized ratio • Serum bilirubin (mg/dl) • Gamma-glutamyltransferase (U/l) • Alkaline phosphatase (U/l) • Amylase (U/l) • Leukocytes (/nl) • Creatinine (mg/dl) • Blood urea nitrogen (mg/dl) • Hemoglobin (g/dl) • Hematocrit (l/l)

#### Radiological assessment

2.3.1

A computed tomography (CT) scan with an arterial phase will be evaluated by the attending radiologist. The focus is on anatomic variations and celiac axis stenosis, which will be classified according to the Michels classification [9]. Examples of important anatomic vessel variations are:•Aberrant right hepatic artery originating from the superior mesenteric artery (Michels type III)•Accessory right hepatic artery originating from the superior mesenteric artery (Michels type VI)•Aberrant common hepatic artery originating from the superior mesenteric artery (Michels type IX)•Aberrant left hepatic artery originating from the left gastric artery (Michels type II)•Right and left hepatic artery originating separately from the celiac trunk

Vessel diameter will also be monitored as it may reveal dilated collaterals due to celiac axis stenosis. To calculate total liver volumes, DICOM files of preoperative CT images (portal phases) were uploaded to the local server and then evaluated using 3D volumetric software AquariusNET (TeraRecon, Inc., Foster City, CA, USA). All eligible participants who give informed consent will be operated and followed up in accordance with the routine procedures of the department of surgery at Heidelberg University Hospital.

#### Intraoperative assessment

2.3.2

During pancreatoduodenectomy, the common/proper hepatic artery and the gastroduodenal artery (and other pancreatoduodenectomy-relevant vessels) will be routinely exposed. A DUPLEX ultrasonography probe will be placed on the artery or vein and peak systolic and diastolic velocities will be measured (these measurements require several cardiac cycles). Blood flow in the relevant vessels supplying the liver will be measured: 1) before the gastroduodenal artery is clamped (after the vessels are prepared), 2) during clamping or after division of the gastroduodenal artery, and 3) before biliodigestive anastomosis (Table 2). To assess the presence of celiac axis stenosis, the direction of the gastroduodenal artery flow will additionally be documented during the first measurement session. The negative flow shows that whether the blood flow is anterograde or retrograde. In the case of negative (retrograde) flow, the percentage of the flow will be also documented. Vital parameters including systolic and diastolic blood pressure, mean arterial pressure, pulse rate, and central venous pressure will be also documented simultaneously to blood flow rate measurements. The dosage of catecholamine administered during blood flow measurements will also be recorded. Arterial blood gas, amount of infusions, operation duration, blood loss, and intraoperative complications will also be monitored.

**Table 2 t0010:** Times of blood flow measurement during the operation.

	Time of measurement	Localization of the measuring sensor	Measuring period
I.	Before clamping the gastroduodenal artery (after preparing the vessels)	Gastroduodenal artery, proper hepatic artery, and portal vein	I (~2 min)
II.	During clamping or after division of the gastroduodenal artery	Proper hepatic artery and portal vein	
III.	Before biliodigestive anastomosis	Proper hepatic artery and portal vein	II (~1 min)

### Outcomes

2.4

#### Primary endpoint

2.4.1

The primary endpoint is arterial flow in the proper hepatic artery, gastroduodenal artery, and in additional liver arteries (in anatomical variations) during pancreatoduodenectomy. In order to obtain valid data that reflects blood flow in the hepatic artery during pancreatoduodenectomy, it will be important to execute the planned measurements before and during clamping or after division of the gastroduodenal artery (mL/min) for 2 minutes during each measurement session.

#### Secondary endpoints

2.4.2

Secondary endpoints aim at the clinical relevance of blood flow rates for liver perfusion, liver-related complications and other complications (Table 3). As liver perfusion failure cannot be directly measured and quantified, it will be assessed using laboratory surrogate parameters for hepatocellular injury and liver function (Table 1, Table 3). Other post-pancreatoduodenectomy complications will be assessed according to the international accepted definitions [6], [10], [11], [12] (Table 3).

**Table 3 t0015:** Secondary endpoints of the HEPARFLOW study.

Endpoints	Definitions
Laboratory findings	Presented in Table 1
Liver volumetric assessment	Total liver volumes (cm^3^) will be evaluated using preoperative computed tomography scans
Length of intensive care unit stay	Time (days) from the day of the operation until the day of discharge from the intensive care unit
Length of hospital stay	Time (days) from the day of the operation until the day of discharge
Liver ischemia following pancreatic resection	According to Hackert et al. [6]
Posthepatectomy liver failure	Based on the ISGLS criteria [12]
Postoperative pancreatic fistula	Based on the ISGPS criteria [10]
Postoperative complications	Graded according to the Clavien–Dindo classification[11]
Mortality	Death due to any cause at any time during the follow-up period

The study may reveal the hemodynamic and clinical relevance of CT morphological compression of the celiac axis during pancreatoduodenectomy. To evaluate the relationship between intraoperative blood flow and liver volume, total liver volume will be calculated based on preoperative CT imaging. The postoperative course, including laboratory analysis and recorded complications on the first day, third day, fifth day, and the day before or on the day of discharge will be documented. The duration of intensive care unit and overall hospital stay will also be recorded (Fig. 2). The classification of liver ischemia following pancreatic resection will be used to demonstrate liver perfusion failure [6]. Posthepatectomy liver failure and postoperative pancreatic fistula will be diagnosed and categorized based on the International Study Group of Liver Surgery (ISGLS) [12] and the International Study Group of Pancreatic Surgery (ISGPS) [10] criteria, respectively. All postoperative complications will be documented. Complications will be graded based on the Clavien–Dindo classification [11]. Perioperative mortality will be registered and mortality will be ascertained after 90 days by phone (Fig. 2).

**Fig. 2 f0010:**
[figure not shown]
Diagram showing the perioperative visit plan of patients in the HEPARFLOW study.

### Patient and public involvement

2.5

The patients and public were not involved in the planning of this study.

### Data collection and management

2.6

Data will be collected until 100 patients are included in the study and all HEPARFLOW measurements are completed. For each subject, a paper-based case report form (CRF) will be filled out. CRFs will be signed by the entering physician. Signed forms and data files will be sent to the trial coordinator. Data completeness will be controlled after each measurement by the investigators and collaborating team. All data will be screened and missing data will be obtained from the study database or from the participant. Each CRF will be assigned an anonymous allocation number to ensure patient confidentiality. Protocol amendments will be considered by the principal investigator.

### Statistical design and analysis

2.7

#### Sample size calculation

2.7.1

For this exploratory study, the sample size cannot be determined as no previous data is available to assume a difference. The aim of this exploratory pilot study is to generate preliminary data to allow sample size calculation in future studies on liver perfusion alterations due to surgery on the hepatic artery or celiac trunk. Based on the previous experiences, blood flow rate measurements from 100 patients will provide enough information about blood flow, also in patients with celiac axis stenosis caused by extrinsic compression from the median arcuate ligament. This condition affects around 10% of patients undergoing pancreatoduodenectomy according to the literature [13], [14], [15], [16].

#### Statistical analysis plan

2.7.2

Descriptive statistics will include mean, standard deviation, minimum, median, maximum, and quartiles for continuous data, and absolute and relative frequencies for categorical data. The empirical distribution of blood flow will be visualized by histograms. Correlation coefficients will be calculated to show possible associations between blood flow and continuous baseline data and postoperative laboratory values. Possible differences between patients with and without postoperative complications will be calculated using the Wilcoxon rank-sum test. Multivariable binary logistic regression will be used to identify possible risk-factors of complications. Because the trial is explorative, all generated p-values must be treated as descriptive. Wherever appropriate, statistical graphics including histograms, scatterplots, and boxplots will be provided to visualize the findings. The significance level will be set at α < 0.05, representing 95% confidence interval.

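### The planned correlations of blood flow with postoperative laboratory values make no use of the preoperative value of the same test, which can dilute the association, or confound it if flow is related to that value

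*Protocol article*

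**What the plan says.** All references are to the protocol article.

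- **Analysis (2.7.2).** "Correlation coefficients will be calculated to show possible associations between blood flow and continuous baseline data and postoperative laboratory values". No change from baseline, partial correlation or baseline covariate is stated. The only multivariable model named in that section is a binary logistic regression, and its outcome is complications, not laboratory values.
- **Role of the laboratory values (2.4.2).** "As liver perfusion failure cannot be directly measured and quantified, it will be assessed using laboratory surrogate parameters for hepatocellular injury and liver function".
- **Which tests.** Before surgery: "Preoperative assessment, including medical history, physical examination, and laboratory evaluations, will be performed according to Table 1". The laboratory row of Table 3 (secondary endpoints) defines its content as "Presented in Table 1". The same tests are therefore taken before and after the operation. They include AST, ALT, albumin, INR, bilirubin, GGT and alkaline phosphatase.
- **When (2.4.2, text after Table 3).** Postoperative values are documented "on the first day, third day, fifth day, and the day before or on the day of discharge".
- **Who enters (2.2.1).** Patients with "bilirubin levels ≥ 15 mg/dl" are excluded, as are those with cirrhosis or other severe liver disease. No limit is set for AST, ALT, GGT or alkaline phosphatase.

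**The concern.** A laboratory value after surgery reflects both what the operation did and where the patient started. The eligibility rules leave room for a wide range of starting values: any bilirubin below 15 mg/dl, and transaminases and cholestatic enzymes without a limit. Whatever part of the postoperative value carries over from before the operation was there before the gastroduodenal artery was clamped, so it cannot be an effect of clamping.

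A two-variable correlation can go wrong in two ways:

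- **Dilution.** If flow is unrelated to the preoperative value, the carried-over variation acts as noise and pulls the coefficient towards zero.
- **Confounding.** If flow is related to the preoperative value, the coefficient also picks up that relation. It may then hide an effect of flow or suggest one that is absent.

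At stake is the trial's laboratory evidence on whether lower flow goes with liver injury. Section 2.7.1 says the study is to supply preliminary data for sizing later studies, so a distorted coefficient could be carried into their design.

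**Working it through.** The article gives no figure to reproduce here. Section 2.7.1 says that a sample size could not be determined, and it states no effect size, standard deviation or power.

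**Inputs**

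- From the article: n = 100 (2.2, 2.7.1) and a significance level of 0.05 (2.7.2), taken as two-sided because sidedness is not stated.
- Assumed, because the article gives none of them:
  - ρ, the correlation of the preoperative with the postoperative value: 0.3 to 0.8
  - a, the correlation of flow with the preoperative value
  - p, the partial correlation of flow with the postoperative value given the preoperative value

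**Relation between the two coefficients**

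Unadjusted r = a·ρ + p·√[(1 − a²)(1 − ρ²)].

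**1. Dilution (a = 0)**

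Here p = r / √(1 − ρ²), and adjustment removes a share ρ² of the outcome variance. Take an unadjusted r of 0.20. The chance that the 95% interval excludes zero follows from Fisher's z as Φ(|atanh r|·√(n − 3) − 1.96), the opposite tail being negligible.

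Unadjusted: atanh(0.20) = 0.2027; 0.2027 × √97 = 1.997; 1.997 − 1.96 = 0.037; chance 51%.

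| ρ | Variance removed (ρ²) | Partial r | Chance interval excludes zero |
|---|---|---|---|
| 0.3 | 9% | 0.20/0.954 = 0.21 | 55% |
| 0.5 | 25% | 0.20/0.866 = 0.23 | 64% |
| 0.7 | 49% | 0.20/0.714 = 0.28 | 81% |
| 0.8 | 64% | 0.20/0.600 = 0.33 | 93% |

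Allowing one degree of freedom for the covariate (n − 4 in place of n − 3) lowers these chances by less than half a percentage point.

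The same point from the other side: fix p at −0.30. The unadjusted r is then −0.29, −0.26, −0.21 and −0.18 at ρ = 0.3, 0.5, 0.7 and 0.8. The chance of an interval excluding zero is 83%, 75%, 57% and 43%, against about 86% with adjustment.

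**2. Confounding (a ≠ 0), for illustration only**

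- No effect of flow (p = 0), a = 0.3, ρ = 0.7: unadjusted r = 0.3 × 0.7 = 0.21. Its interval would exclude zero in about 56% of such trials. With adjustment, simulation of 10,000 trials gave 4.6%.
- True effect p = −0.30, a = 0.3, ρ = 0.7: unadjusted r = 0.21 − 0.30 × √(0.91 × 0.51) = 0.21 − 0.204 = 0.006. The effect disappears. Simulation gave 4.8% of intervals excluding zero unadjusted and 85.7% adjusted.
- No effect and a = 0: unadjusted r = 0, with the usual 5%. A spurious association needs a link between flow and the preoperative value.

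**The case against.** **The article is condensed, and one sentence does not rule out adjustment.** The text does not fix the coefficient or the scale, so calling the correlation unadjusted is a reading of unqualified wording. It is nevertheless the natural reading: the method is named, and the one multivariable model is assigned to another outcome. The point is directed at the stated method, which can be improved at almost no cost.

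**The baseline values are not ignored.** This stands. The same sentence correlates flow with continuous baseline data, which can include the preoperative laboratory values in Table 1. The relation that would cause confounding can therefore be seen. What is missing is a step that carries it into the postoperative comparison.

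**The analysis is exploratory and its p-values are descriptive.** This limits the weight of the point, and the chances of excluding zero decide nothing in this trial. The label does not remove dilution or confounding from the coefficient itself.

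**Perfusion failure does not rest on these correlations alone.** This also stands. Section 2.4.2 uses a liver ischemia classification for the same purpose.

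**Stronger readings that the article does not support.** A reader might infer any of the following:

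- *The planned correlations will mask or mimic an effect of flow.* Dilution is slight at ρ = 0.3, and mimicking needs a flow–baseline link that the article does not quantify.
- *Most of the variance in the postoperative values is preoperative disease.* That requires ρ above about 0.71 (ρ² > 0.5), and no such figure is given.
- *Discharge values are biased because longer stays go with worse courses.* The article does not say so. It shows only that the day of the sample differs between patients, and it does not say that this value will be correlated with flow.

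**Conclusion.** The point holds as a limited improvement to a secondary, exploratory analysis. As stated, 2.7.2 relates flow to postoperative laboratory values without the preoperative value of the same test, which the trial already collects. Dilution follows whenever the two values are correlated. Its size depends on an assumed correlation, which may differ from test to test: next to nothing at 0.3, moderate at 0.5, substantial at 0.7 or more. Confounding is possible but conditional on flow being related to the preoperative value. The illustrations above show what it could do, not what it will do here. The primary endpoint, the description of arterial flow, is unaffected.

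**What to change.** Add to 2.7.2 that, for each laboratory test and separately at postoperative days 1, 3 and 5:

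- the association with flow will be estimated with adjustment for the preoperative value of that test, either by regression with both laboratory values on the log scale or by partial Spearman correlation given the preoperative value;
- the slope or partial correlation will be reported with a 95% confidence interval;
- the unadjusted coefficient will be kept as a supplement.

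The discharge value, whose timing differs between patients, should be reported descriptively.

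The cost is a sentence or two in 2.7.2 and a few lines of analysis code. No further measurements, visits or patients are needed.

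### Unpenalised multivariable logistic regression in 100 patients can overstate odds ratios for complications; Firth's method costs little and avoids most of the bias

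*Protocol article*

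**What the plan says.** Section 2.7.2 of the protocol article gives one sentence to this analysis: "Multivariable binary logistic regression will be used to identify possible risk-factors of complications". It adds that "Because the trial is explorative, all generated p-values must be treated as descriptive".

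The sample is fixed in section 2.2: "All consecutive patients undergoing elective pancreatoduodenectomy will be screened for inclusion until 100 patients are enrolled". Section 2.7.1 explains that this number does not come from a calculation: "For this exploratory study, the sample size cannot be determined as no previous data is available to assume a difference". No event rate for any complication is given.

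The article records overlapping measurements that could serve as covariates. In Table 2 the first session covers "Gastroduodenal artery, proper hepatic artery, and portal vein", and the proper hepatic artery and portal vein are read again in the second and third sessions. Section 2.3.2 also records systolic, diastolic and mean arterial pressure at the time of each flow measurement. The article does not say which of these, or how many covariates, enter the logistic model.

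**The concern.** The maximum likelihood estimate of a log odds ratio is biased away from zero in small samples. The bias grows as the number of events per covariate falls. With very few events the fit may separate, so that no finite estimate exists.

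Here the number of patients with the outcome is at most a part of 100, and for rarer outcomes such as liver ischemia or liver failure it may be small. What is at stake is the odds ratio reported for each possible risk factor, including hepatic artery flow. Readers would take it as the strength of the association, and it could be too large. Entering several readings of the same vessel, or three pressures that largely determine one another, would make the estimates less stable still.

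**Working it through.** The plan has no figure of its own to reproduce: there is no event rate, covariate count or assumed effect. The check is therefore a simulation over assumed values.

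**Inputs**
- N = 100 (section 2.2).
- Model: multivariable logistic regression, no penalty stated (section 2.7.2).
- Assumed: 5 to 50 events and 2 to 10 predictors. Predictors are independent and standard normal. One has a true odds ratio of 2.0 per SD, so log 2.0 = 0.69; the others have no effect.
- About 600 simulated data sets per setting, each fitted by maximum likelihood (ML) and by Firth's penalised likelihood. ML means use converged fits only.

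**Formulas**
- Events per predictor = events / predictors.
- Relative bias = (mean log odds ratio − 0.69) / 0.69.
- Odds ratio shown = exp(mean log odds ratio).

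**Results**

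| Events (assumed) | Predictors | Events per predictor | ML mean log OR | exp | Relative bias | Firth mean log OR |
|---|---|---|---|---|---|---|
| 30 to 50 | 2 to 5 | 6 to 25 | 0.71 to 0.77 | 2.03 to 2.16 | +3% to +12% | within 0.62 to 0.71 |
| 30 to 50 | 10 | 3 to 5 | 0.80 to 0.82 | 2.23 to 2.27 | +16% to +19% | within 0.62 to 0.71 |
| 40 | 10 | 4 | 0.80 | 2.23 | +16% | 0.69 |
| 20 | 5 | 4 | 0.79 | 2.20 | +14% | 0.71 |
| 10 | 10 | 1 | 0.94 | 2.56 | +36% | 0.68 |
| 5 | 10 | 0.5 | 120 of about 600 fits failed (20%) | – | – | within 0.62 to 0.71 |

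Example for the fifth row: (0.94 − 0.69) / 0.69 = 0.25 / 0.69 = 36%, and exp(0.94) = 2.56.

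Over all settings the Firth mean lies at about 0.62 to 0.71, a relative bias of −10% to +3%. Its root mean squared error was lower than that of ML in every setting, so the gain in bias is not paid for in precision.

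Simulation noise is about 0.02: two runs with 40 events and 10 predictors gave ML means of 0.80 and 0.82, with Firth at 0.69 and 0.71.

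The predictors were independent. Correlated laboratory or flow values would make the ML estimates less stable.

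**The case against.** The strongest reply is that logistic regression is a standard method for a binary outcome, that the study is a declared exploratory pilot with descriptive p-values, and that a covariate list and selection rule may stand in a fuller plan that is not shown. With a short list and enough events, ML does well: with 3 to 5 predictors and 20% to 50% events, a true odds ratio of 1.5 was estimated at a median of 1.50 to 1.61.

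Most of this stands. The missing covariate list is not itself a fault of a journal article, and the bias is small under favourable counts. The exploratory label does not answer the point, because the bias lies in the estimate and remains if no p-value is printed.

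Three stronger readings are tempting, and the documents do not support them:
- **That everything recorded will be searched.** A reader could count 27 items in Table 1 ("Preoperative parameters to be evaluated in included patients": 7 + 5 + 2 + 13), 20 intraoperative items and 4 from CT, 51 in all. The article never says that these are candidates for the model. It gives several of them other uses: liver volume is to be related to flow, laboratory values are also endpoints, and flow against continuous baseline data is assigned to correlation coefficients.
- **That the model will appear to predict well by chance.** No prediction model or measure of discrimination is planned.
- **That a later study will be sized on this odds ratio.** Section 2.7.1 speaks of preliminary data for future studies of liver perfusion alterations and does not name the odds ratio as the input.

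**Conclusion.** The point holds in a conditional form. The article names an estimator that is biased away from the null at this sample size, and a better one is available in standard software. The expected inflation of the log odds ratio is about 3% to 12% with 2 to 5 predictors and 30 to 50 events, 16% to 19% with 10 predictors and the same events, and 36% with 10 predictors and 10 events. With 5 events and 10 predictors about one fit in five fails.

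These figures rest on assumed event counts, predictor numbers and a true odds ratio of 2.0 per SD, none of which the article gives. It would be wrong to say that the odds ratios will be badly inflated; that depends on choices the article does not state. Firth's method did better in every setting tried, so the change is worthwhile whichever applies.

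**What to change.** Replace the logistic regression sentence in section 2.7.2 with wording such as:

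> Possible risk factors of complications will be explored with Firth-penalised multivariable logistic regression and profile-likelihood 95% intervals. A short covariate list, fixed before outcomes are seen, will include proper hepatic artery flow at one named reading. Repeated readings of one vessel will not be entered together, nor will systolic, diastolic and mean pressure.

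The short list is part of the remedy because the bias grows with the number of covariates.

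The cost is a change of wording and the use of standard software, with no extra patients or data. The downside is that fewer factors are examined jointly; the others can be reported one at a time.
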